# Dedicated MRI staging versus surgical staging of peritoneal metastases in colorectal cancer patients considered for CRS-HIPEC; the DISCO randomized multicenter trial

**DOI:** 10.1186/s12885-021-08168-x

**Published:** 2021-04-26

**Keywords:** Colorectal peritoneal metastases, CRS-HIPEC, Surgical staging, MRI, RCT

## Abstract

**Background:**

Selecting patients with peritoneal metastases from colorectal cancer (CRCPM) who might benefit from cytoreductive surgery followed by hyperthermic intraperitoneal chemotherapy (CRS-HIPEC) is challenging. Computed tomography generally underestimates the peritoneal tumor load. Diagnostic laparoscopy is often used to determine whether patients are amenable for surgery. Magnetic resonance imaging (MRI) has shown to be accurate in predicting completeness of CRS. The aim of this study is to determine whether MRI can effectively reduce the need for surgical staging.

**Methods:**

The study is designed as a multicenter randomized controlled trial (RCT) of colorectal cancer patients who are deemed eligible for CRS-HIPEC after conventional CT staging. Patients are randomly assigned to either MRI based staging (arm A) or to standard surgical staging with or without laparoscopy (arm B). In arm A, MRI assessment will determine whether patients are eligible for CRS-HIPEC. In borderline cases, an additional diagnostic laparoscopy is advised. The primary outcome is the number of unnecessary surgical procedures in both arms defined as: all surgeries in patients with definitely inoperable disease (PCI > 24) or explorative surgeries in patients with limited disease (PCI < 15). Secondary outcomes include correlations between surgical findings and MRI findings, cost-effectiveness, and quality of life (QOL) analysis.

**Conclusion:**

This randomized trial determines whether MRI can effectively replace surgical staging in patients with CRCPM considered for CRS-HIPEC.

**Trial registration:**

Registered in the clinical trials registry of U.S. National Library of Medicine under NCT04231175.

## Background

Peritoneal metastatic disease is the dissemination of cancer within the abdominal cavity. It is the second leading cause of death in patients with colorectal cancer (CRC). 10.6% of CRC patients present with peritoneal metastases at diagnosis or will develop peritoneal metastases at a later stage [1]. Selected patients benefit from cytoreductive surgery (CRS) followed by hyperthermic intraperitoneal chemotherapy (HIPEC). CRS-HIPEC is potentially curative and has shown to improve median survival in patients with limited disease [2–4]. Macroscopically complete resection of all metastatic lesions is vital to obtain survival gain [5]. Currently, assessment of the extent and localization of peritoneal metastases, to determine whether a complete CRS is feasible, is ultimately performed during laparotomy. Open-close or incomplete procedures have been reported to occur in 20 to 40% of cases [6–11]. However, best practice would be to avoid futile, invasive and costly surgical procedures in patients for whom CRS-HIPEC is not feasible and/or unlikely to improve survival. Laparoscopic assessment is a less invasive and effective tool to reduce futile laparotomies [9]. However, tumor mass or adhesions may prevent laparoscopic evaluation of all regions of the peritoneal cavity. Incomplete laparoscopic staging has been reported to occur in around 23% of patients [6]. Laparoscopy is considered minimally invasive but a risk of intraoperative complications and postoperative morbidity presides. Hence, a non-invasive pre-operative tool is needed to better select patients eligible for CRS-HIPEC.

CT is the preferred first-line imaging tool for the detection of peritoneal metastases but falls short when used to assess the total peritoneal tumor burden [12–16]. Magnetic resonance imaging (MRI), with diffusion-weighted imaging (DWI), has shown to predict the extent of disease accurately (sensitivity of 0.80–0.98 and a specificity 0.85–0.93% [17, 18]) and to be a valuable adjunct to decide whether complete cytoreduction can be achieved [13, 15, 17]. DWI-MRI had also shown to be superior for detecting liver metastases [19, 20]. However, research towards the value of MRI for patients with colorectal peritoneal metastases has been limited to cohort studies in a retrospective or observational setting.

### Objective

The primary objective of this study is to determine whether additional preoperative dedicated MRI staging to can reduce the number of futile (exploratory) surgeries in patients with CRC considered for CRS-HIPEC as compared to the standard of care of CT alone. An unnecessary surgical procedure is defined as any non-therapeutic laparotomy or diagnostic laparoscopy in patients, with exception of patients with borderline operable disease (15<PCI> 24).

## Methods/design

This investigator-initiated, multi-center, randomized controlled trial is performed in Dutch HIPEC centers since September 2019. The study is conducted according to the principles of the Declaration of Helsinki and in accordance with the Medical Research Involving Human Subjects Act (WMO) and was approved by the medical ethics committee at the Netherlands Cancer Institute (date: 13-09-2019; ref. no.: NL70045.031.19) and is retrospectively registered in the clinical trials registry of U.S. National Library of Medicine under NCT04231175 (https://clinicaltrials.gov/ct2/show/NCT04231175). Patients suspected of having CRC peritoneal metastases and considered for CRS-HIPEC, are eligible for inclusion. Patients are randomly assigned to one of two diagnostic arms towards CRS-HIPEC. A trial flow diagram is presented in Fig. 1.

**Fig. 1 Fig1:**
[figure not shown]
Flow diagram of DISCO trial

### Eligibility criteria

In order to be eligible to participate in this study, a subject must meet all of the following criteria:
Patients with suspicion of CRCPM and considered for CRS-HIPEC after CT imagingAge ≥ 18 yearsWritten and signed informed consentPerformance status of WHO 0–2Able and willing to drink 1 l of pineapple or blueberry juice (required as a preparatory step for the dedicated MRI)

A potential subject who meets any of the following criteria will be excluded from participation in this study:
Patients with contraindications for MRIPatients with clinical contraindications for CRS-HIPEC, such as but not limited to inadequate organ or hematological function, significant medical history, active pregnancy and lactation, or old agePatients with radiological contra-indications for CRS-HIPEC observed on CT thorax/abdomenPatients with concurrent or history of other malignancy within ≤5 years prior to CRCPM diagnosis

### Patient recruitment and randomization

Eligible patients are identified and informed about the study by their treating physician at the participating center. Patients are included after written informed consent. Patients are randomly assigned to an experimental arm (A) or a control arm (B). The random assignment is performed by dedicated medical data managers or a research nurse using specific clinical trial management software (ALEA clinical, Abcoude, The Netherlands). A random block randomization is used and stratified per participating center. Blinding is not possible with this trial set-up.

### Study interventions

Patients in Arm A receive a dedicated 3 T MRI scan, which includes T2 weighted, T1 weighted, diffusion weighted and non-enhanced + gadolinium enhanced fat-suppressed T1 weighted imaging of the pelvis and abdomen (and thorax on DWI), as previously described [15]. Patients are asked to drink one liter of pineapple or blueberry at least 1 h before the MRI scan. This minimizes the signal from the intraluminal content on DWI and bowel movement, respectively. An antispasmolitic drug is administered intravenously to optimize bowel evaluation. The MRI protocol is specified in Table 1. Based on the findings of the MRI scan, the radiologist advises whether patients are to be allocated to one of the following diagnostic/treatment options:
CRS-HIPEC is feasible; perform CRS-HIPEC
○ Peritoneal cancer index estimated on MRI (MRI-PCI) < 15 and no non-peritoneal lesions (that contra-indicate CRS-HIPEC)CRS-HIPEC might be feasible; consider diagnostic laparoscopy (DLS) to determine whether CRS-HIPEC is feasible and justifiable
○ MRI-PCI between 15 and 24 and no non-peritoneal lesions (that contra-indicate CRS-HIPEC)CRS-HIPEC is not feasible; chemotherapy or best supportive care
○ MRI-PCI > 24 and/or detection of non-peritoneal lesions (that contra-indicate CRS-HIPEC)

**Table 1 Tab1:** Dedicated MRI protocol for peritoneal surface malignancies

	Diffusion weighted	T2 weighted		T1 weighted		
				Pre-contrast	Post-contrast	Post contrast
Pulse sequence	SS EPI b0, b1000	SS TSE	SS TSE	mDixon 3D FFE	mDixon 3D FFE	mDixon 3D FFE
Imaging plane	Transversal	Transversal	Coronal	Transversal	Transversal	Coronal
Anatomical area	Thorax, abdomen, pelvis	Abdomino-pelvic	Thorax, abdomen, pelvis	Abdomino-pelvic	Abdomino-pelvic	Abdomino-pelvic
Respiration	Free-breathing	Free-breathing	Free-breathing	Free-breathing	Free-breathing	Free-breathing
Fat supression	SPIR	–	–	SPAIR	SPAIR	SPAIR
TR/TE (ms)	Shortest	1500/87	1500/87	Shortest	Shortest	Shortest
NSA	1	1	1	1	1	1
Slice thickness (mm)	5	4	6	5	5	5
Gap (mm)	0.5	0.4	0.6	−2.5	−2.5	−2.5

In the Netherlands, patients are eligible for CRS-HIPEC if the PCI does not exceed 20 at surgical exploration [21]. All participating centers perform CRS-HIPEC procedures under the Dutch HIPEC protocol, as described by Kuijpers and colleagues [21]. With this policy in mind, the cut-off points for MRI-assessment have been determined using preliminary data of the initiating center [15]. The MRI-PCI cut-off of 15 ensures targeted use of DLS and the cut-off of 24 prevents the false omission of patients for whom CRS-HIPEC is feasible. If a specific disease localization is found which could contraindicate CRS-HIPEC, i.e. duodenal involvement, DLS may still be performed at the discretion of the multidisciplinary team (MDT). Surgical procedures must be performed within 4 weeks after the MRI.

In arm B, patients undergo the standard diagnostic work-up followed by a DLS at the discretion of the MDT, as determined before randomization. For the control group no study specific guidelines for DLS use have been determined, centers are expected to continue implementing DLS according to their own current policies. The rate of laparoscopy use may therefore vary between centers.

All patients will be asked to fill in two QOL questionnaires (EORTC-C30 and EQ5D5L) at baseline (randomization), at 3 months, and 6 months. At 6 months after CRS-HIPEC, all patients undergo a follow-up of CT, MRI, serum biomarkers (carcinoembryonic antigen or CEA, cancer antigen 125 or CA 125, and cancer antigen 19.9 or CA 19.9), and physical examination to screen for early disease recurrence in the peritoneum, liver, or elsewhere. This will also serve as an extra quality check of diagnostic and surgical outcome. It is expected that a residual peritoneal or non-peritoneal metastasis will have become apparent at 6 months on MRI. If residual disease of early recurrence is observed, treatment is at the discretion of the local MDT. The trial schedule is summarized in Table 2.

**Table 2 Tab2:** Schedule of enrolment, interventions, and assessments

STUDY PERIOD						
	Enrolment	Allocation	Diagnostic Work-up	Treatment	Follow-up	
TIMEPOINT^b^	***-T***_***1***_	T_**0**_	T_**1**_	T_**1**_	***T***_***3***_	***T***_***6***_
**ENROLMENT:**						
**Eligibility screen**	X					
**Informed consent**	X					
**Allocation**		X				
**INTERVENTIONS**						
***MRI***			A			X^b^
***Diagnostic laparoscopy***			B^a^/A^a^			
***CRS-HIPEC***				A^a^/B^a^		
**ASSESSMENTS**						
***QUALY forms***		X			X	X

X applicable to all patients; A applicable to those allocated to experimental Arm A; B applicable to those allocated to control arm B

^a^ only applicable if called for by previous diagnostics

^b^ only applicable if R1 resection was achieved at CRS-HIPEC

### MRI evaluation

All study MRIs will be evaluated by an abdominal radiologist with experience in DWI of the participating center and by experienced abdominal radiologists of the trial-initiating center with extensive experience with the study protocol dedicated to peritoneal metastasis evaluation, independently. The findings of the radiologists then will be shared and discussed before the MDT meeting. In case of discrepant findings, the findings from the trial-initiating center’s radiologist are leading. Radiologists of the participating centers will undergo training in the study specific MRI evaluations, followed by on-the-job training with continued feedback of the trial-initiating center.

Criteria used to establish the presence of peritoneal disease on MRI include the presence of high signal on DWI with a corresponding soft tissue lesion of peritoneal thickening on T2 weighted or contrast enhanced T1 weighted images, as previously described [15].

### Data collection

Basic clinical information is collected, including patient history, primary tumor location, tumor histology, previous surgical procedures, chemotherapy and/or radiotherapy history, and serum biomarkers. For each abdominal assessment preformed to assess eligibility for CRS-HIPEC (CT, MRI, laparoscopy, and laparotomy), a case report form (CRF) is filled out including the same parameters for each assessment, where appropriate. These parameters include the PCI, the presence of organ infiltration, the presence and pattern of miliary spread, presence of non-PM (such as liver and lymph node metastases) and diaphragmatic involvement. Parameters specific to radiological assessments (CT, MRI) include scan quality, scan completion, presence of extra abdominal metastases (retroperitoneum, chest), and presence of pleural effusion. For each radiological finding, the reader will indicate whether the feature is present (yes/no) and how certain he or she is of that decision (not certain/ quite certain/ certain). Parameters specific to surgical assessment include extent of adhesiolysis and accessibility. Surgical findings are considered the reference standard. No confidence level will be applied to those parameters. For the laparotomies that proceed to CRS-HIPEC, a separate CRF registers which resections, excisions, and/or extirpations have been performed, as well as the completeness of cytoreduction (resection status). All data is collected by the local research team, consisting of at least one radiologist, one surgeon, and a research nurse and/or medical data manager. The pseudo-anonymized data is entered and stored with the same clinical trial management software used for randomization (ALEA clinical, Abcoude, The Netherlands) in an ISO 27001 certified hosting facility in the Netherlands.

### Outcome measures

The primary outcome measure is a composite endpoint of futile surgical explorations. A futile surgical exploration is defined as: all surgeries in patients with definitely inoperable disease (PCI > 24) or explorative surgeries in patients with limited disease (PCI < 15).

The secondary outcomes include:
number of incomplete CRS-HIPECs (R2a/ R2b/ open-close),number of residual disease events or early recurrences at 6 months after a complete resection at CRS-HIPEC,number of non-peritoneal metastases,diagnostic performance of MRI and diagnostic laparoscopy to predict whether complete CRS-HIPEC is feasible,correlations between MRI findings and surgical findings,incremental cost-effectiveness,Patient reported QOL between study arms.

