### Data analysis

The observed difference in preventable surgical explorations between trial arms will be tested with a McNemar’s chi-squared test, as well as the difference in incomplete CRS-HIPECs, non-peritoneal findings before surgery, and early recurrences or residual disease visible at first follow-up (6 months). Progression free survival will be analyzed by binomial logical regression analysis. Progression free survival is defined as the time in days from complete CRS-HIPEC to recurrence or progression of disease as determined by the multidisciplinary team meeting or death of any cause. Correlations between MRI staging and surgical staging will be evaluated by intraclass correlation coefficients (ICC), Cohen’s kappa, and Cohen’s weighted kappa, where appropriate. Diagnostic performance of MRI and surgical staging to predict complete CRS will be compared by confusion matrix analysis and receiver operator characteristic analysis. Differences in predictive values will be tested with McNemar’s test and the DeLong test, where appropriate.

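### Early recurrence is tested between arms only among completely resected patients, a subset that the allocated staging strategy selects, so this secondary comparison is open to selection bias

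*Protocol article*

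**What the plan says.** All references are to the Protocol article.

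- **Outcome.** The Outcome measures section lists the "number of residual disease events or early recurrences at 6 months after a complete resection at CRS-HIPEC". Patients without a complete resection cannot contribute an event.
- **Test.** The Data analysis section says "The observed difference in preventable surgical explorations between trial arms will be tested", and the same sentence extends the test to other outcomes, among them "early recurrences or residual disease visible at first follow-up (6 months").
- **PFS.** The same section states: "Progression free survival will be analyzed by binomial logical regression analysis". It then fixes the time origin: "Progression free survival is defined as the time in days from complete CRS-HIPEC to recurrence or progression of disease". PFS is not in the list of secondary outcomes, and no arm contrast is written for it.
- **Who enters the subset.** The abstract's Methods paragraph says "In arm A, MRI assessment will determine whether patients are eligible for CRS-HIPEC". Study interventions gives the arm A rules: an MRI-PCI above 24, or non-peritoneal lesions that contraindicate the procedure, leads away from CRS-HIPEC. For arm B it sets no study-specific rule for laparoscopy and leaves its use to each centre's policy.
- **Six-month follow-up.** Study interventions says "At 6 months after CRS-HIPEC, all patients undergo a follow-up of CT, MRI, serum biomarkers". The Table 2 footnote makes the 6-month MRI "only applicable if R1 resection was achieved at CRS-HIPEC".

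**The concern.** Randomisation makes the arms comparable as allocated. It does not make comparable the patients in each arm who later had a complete resection, because selection for CRS-HIPEC is the very thing the two strategies do differently. If one strategy steers more high-burden patients away from surgery, its resected group will have a better prognosis whatever that strategy does for any individual. If it brings more extensive disease to complete resection, its resected group will look worse.

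The document gives no version of either outcome over all randomised patients, no time origin at randomisation and no adjustment for selection. What it does fix (the population, the between-arm test and the PFS clock) produces the problem, so this is not a detail left to an analysis plan.

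The stake is interpretation. The primary outcome counts futile surgery and does not register a feasible resection that was withheld. Early recurrence and PFS also exclude any patient from whom a feasible resection was withheld. A favourable subset result could be read as reassurance about MRI staging when it shows only a differently selected group.

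**Working it through.** **Plan's own figures.** There are none to reproduce: the document gives no rates, effect size or power for early recurrence or PFS. All rates below are assumed. Its total of 272 patients is used only to set 136 per arm, assuming 1:1 allocation.

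**Illustration 1 (assumed), 100 patients per arm.** Arm B completes resection in 60: 54 with a 25% risk of early recurrence and 6 with a 60% risk. Arm A completes resection in the same 54 only. No patient's risk after resection differs by arm.

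| | Arm A | Arm B |
|---|---|---|
| Recurrences | 54 × 0.25 = 13.5 | 54 × 0.25 + 6 × 0.60 = 17.1 |
| Rate among complete resections | 13.5/54 = 25.0% | 17.1/60 = 28.5% |
| Complete and recurrence-free, per 100 randomised | 54 − 13.5 = 40.5 | 60 − 17.1 = 42.9 |

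The subset favours A by 3.5 points; the all-randomised comparison favours B by 2.4 points.

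**Changing only the denominator does not help.** Recurrences per 100 randomised are 13.5 in A and 17.1 in B. The arm with fewer resections has fewer recurrences automatically.

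**Illustration 2 (assumed), three risk groups.** Mix 55/25/20%; recurrence risk after complete resection 15/35/60%. For each arm, with sums over groups:

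- subset rate = Σ(mix × P(complete) × risk) / Σ(mix × P(complete))
- all-randomised success = Σ(mix × P(complete)) − Σ(mix × P(complete) × risk)

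(a) *Same selection, no effect* (P(complete) 0.95/0.70/0.20 in both arms): 22.2% in each arm, difference 0.

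(b) *No effect, A screens out more* (A 0.95/0.40/0; B 0.95/0.80/0.40):
- A: 0.1134/0.6225 = 18.2%; success 0.6225 − 0.1134 = 50.9%.
- B: 0.1964/0.8025 = 24.5%; success 0.8025 − 0.1964 = 60.6%.
- The subset favours A by 6.3 points; all randomised favour B by 9.7 points.

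(c) *Every risk 10% lower in A, and A completes resection in more extensive disease* (A 0.95/0.85/0.35; B 0.95/0.60/0.10):
- A: 0.1753/0.8050 = 21.8%; success 63.0%.
- B: 0.1429/0.6925 = 20.6%; success 55.0%.
- The subset favours B by 1.1 points although every patient's risk is lower in A.

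Differential selection alone creates the difference in (b), and the distortion can run either way.

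**Size against sampling error.** For illustration 1 at 136 per arm, complete resections number 136 × 0.54 = 73.4 (A) and 136 × 0.60 = 81.6 (B).
- SE of the subset difference: √(0.25 × 0.75/73.4 + 0.285 × 0.715/81.6) ≈ 7.1 points, against a difference of 3.5.
- SE of the all-randomised difference: √(0.405 × 0.595/136 + 0.429 × 0.571/136) ≈ 6.0 points, against 2.4.

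**The case against.** Several objections deserve weight.

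- **The reversal rests on assumed inputs.** This stands. Study interventions says the MRI-PCI cut-off of 24 is meant to avoid wrongly excluding patients in whom CRS-HIPEC is feasible, against a surgical limit of PCI 20, with laparoscopy considered for the borderline range. That is a design aim, not evidence that selection will match between arms, and non-peritoneal lesions on MRI also exclude patients. A reader might infer that the bias will favour MRI; the document does not support any direction.
- **The illustrated differences are small beside their standard errors.** True for illustration 1. Imprecision does not make the comparison a randomised one.
- **The 6-month assessment is described as an additional check on diagnostic and surgical quality, a question that arises only in resected patients.** This supports reporting the subset descriptively. It does not support the between-arm test in Data analysis.
- **A between-arm PFS test is not written.** This stands. A reader might take it as stated because the paragraph opens with arm comparisons, but the contrast is only implied.
- **Timing.** A reader might infer that the PFS clock starts later in arm B because laparoscopy may come first. Arm A may also have a laparoscopy first (MRI-PCI 15 to 24; Table 2 marks it for both arms), so no differential delay is shown.
- **Withholding surgery is not necessarily without benefit.** A reader might infer that screening patients out helps nobody. The Discussion argues that avoiding open-close surgery spares palliative patients harm and delay, so that inference goes too far.

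**Conclusion.** The point holds for early recurrence or residual disease at 6 months. The outcome is conditioned on a post-randomisation event that the allocated strategy influences, and the arms are nevertheless tested on it. The PFS definition has the same restriction, with the between-arm contrast implied only.

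The size and direction of the bias cannot be derived from the document. The figures show that opposite signs are possible (25.0% against 28.5% in the subset, 40.5% against 42.9% per randomised patient), not that they are expected. They rest on assumed risk mixes, resection probabilities and recurrence rates; with identical selection in both arms the bias was zero.

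This should be fixed, but it concerns secondary outcomes only. A reader might extend it to the primary outcome, which is not conditioned on complete resection and is not touched by this point.

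The 6-month imaging wording is a separate and smaller matter. The text in Study interventions reads most naturally as covering everyone who had CRS-HIPEC, whereas the Table 2 footnote limits the MRI to R1 resections. What is unclear is whether patients with an incomplete resection are imaged. They fall outside the early-recurrence outcome, so this does not drive the bias.

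**What to change.** 1. Make the between-arm comparison the proportion of all randomised patients who had a complete resection and are alive without residual or recurrent disease at the 6-month assessment. Count no CRS-HIPEC, or an incomplete one, as not achieved.
2. Show the components by arm: complete resection, then residual or recurrent disease or death among those resected. The composite mixes resection with recurrence, and readers need to see which one drives a difference.
3. Report early recurrence, and PFS from CRS-HIPEC, in completely resected patients as descriptive results without a between-arm p-value.
4. Add a between-arm PFS measured from randomisation only if progression is recorded in unresected patients. The article ties 6-month imaging to CRS-HIPEC and schedules no progression assessment for the others, so this would need additional data and a definition of progression in unresected disease.
5. Reconcile Study interventions with the Table 2 footnote on whether patients with an incomplete resection have the 6-month MRI.

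Items 1 to 3 cost a change of wording and a little extra analysis: resection status is already on the case report form, and the 6-month follow-up after CRS-HIPEC is already planned.
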